### Blinding

For logistical reasons, participants, researchers, and instructors are not blind to the allocation of participants.

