### Aim

The aims of the present study are to:

(1) examine the impact of an exercise training program for older adults on cognitive and physical functioning,

(2) compare the impact of exercise training and a combined program of cognitive *and *exercise training for older adults (which has an equal number of total training sessions per week) on cognitive and physical functioning,

(3) examine associations between changes in aerobic capacity (as a result of exercise) and changes in cognitive functioning;

(4) examine associations between changes in psychological wellbeing (as a result of exercise) and changes in cognitive functioning; and

(5) identify older adults' perceptions of exercise training and combined exercise and cognitive training.

An exercise training program and a cognitive training program have been developed by the first author (SO), and will be evaluated in a randomized controlled trial. The content of these programs is based on previously successful training programs, and current theories regarding the relationships between exercise training, cognitive training, and cognitive functioning.

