### Setting

The program is conducted at *Riverside Fitness*, a privately-owned gym in Brisbane, Australia.

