### Intervention

#### Exercise-only training

Participants in this group receive three gym-based sessions per week for 16 weeks. Each session lasts for 60 minutes and includes progressive aerobic and strength training. Each session includes a maximum of 10 participants and is supervised by at least one qualified fitness instructor.

The progression of the aerobic training is adapted from the ACSM Guidelines for Exercise Testing and Prescription [51]. Intensity is prescribed using percentage of Heart Rate Reserve (HRR). Participants on medications which attenuate heart rate (e.g. beta-blockers) are prescribed exercise intensity using Rate of Perceived Exertion (RPE; [52]). The relative progressions of intensity and duration can be seen in Table 1. Intensity is monitored with Polar A3 heat rate monitors. Participants complete the aerobic training on treadmills, stationary bicycles, cross-trainers, and stationary rowing machines.

**Table 1 T1:** Duration and intensity progression of aerobic training

**Week**	**Duration (min)**	**Intensity (% HRR)**	**Intensity (RPE)**
1	20	50 – 60	9 – 11
2	20	50 – 60	9 – 11
3 – 5	25	60 – 70	11
6 – 8	30	60 – 70	11
9 – 11	30	70 – 80	11 – 13
12 – 14	35	70 – 80	11 – 13
15 & 16	40	75 – 85	13 – 15

Strength is assessed, and intensity prescribed, for each participant in the first gym session. Progress is monitored and prescribed by the fitness instructor. The strength training includes exercises to target major muscle groups in the upper body, lower body, and core. The upper and lower body exercises use free weights and machines. The core exercises use a swiss-ball.

Participants stretch major muscle groups at the end of each session.

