#### Exercise and cognitive training

Participants in this group receive two gym-based exercise sessions and one cognitive training session per week for 16 weeks. Each session lasts for 60 minutes. The exercise training (including the progression of duration and intensity) is identical to that received in the Exercise-Only Group. The cognitive training program includes three modules, covering memory, executive functioning, and mental speed. Each session follows the same format:

(1) theoretical overview

(2) outline of 'everyday' applications

(3) practice activities

Introductory and revision sessions are conducted at the beginning and end of the program. Table 2 outlines the content of each session. A graduate psychology student leads these sessions in a quiet room away from the main gym area.

**Table 2 T2:** Cognitive training program outline

Module	Session	Content
Introduction	1	Aging, Cognitive Functioning, Program Overview
		
Memory	2	Introduction to Memory
	3	Chunking, Organisation, Visualisation
	4	Storytelling, Method of Loci, Mnemonics
	5	Keywords, Association
		
Executive Function	6	Introduction to Reasoning
	7	Pattern Identification
	8	Concept Formation, Verbal Fluency
	9	Attention, Mental Flexibility
		
Information Processing	10	Introduction to Speed of Information Processing
	11	Simple Speed
	12	Choice Response Speed
		
Revision	13	Memory
	14	Executive Function
	15	Speed of Information Processing
	16	General

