#### Modes of assessment

Screening is conducted by telephone. Cognitive and physical assessments are conducted face-to-face at the University of Queensland. Cognitive assessments are conducted by SO. Each cognitive assessment session lasts for 90 minutes. Physical assessments are conducted by an exercise physiologist and last for 30 minutes. Physical assessments are conducted immediately after the cognitive assessments. Self-administered questionnaires are used to assess psychological wellbeing. These are provided after the cognitive assessment, with participants instructed to complete them at home and mail them back within seven days using a provided reply-paid envelope. Participant perceptions of the two training programs are collected using a feedback form included with the other self-report instruments. Only training participants complete this feedback form.

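### The Blinding section makes no exception for the exercise physiologist who does the physical tests, although nothing described requires that assessor to know the allocation

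*Protocol article*

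**What the plan says.** The Blinding section is a single sentence. It says that, on logistical grounds, "participants, researchers, and instructors are not blind to the allocation of participants". It does not mention outcome assessors separately and does not say what the logistical obstacle is.

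Other sections describe who does what, and where:

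- **Physical tests.** Modes of assessment says "Cognitive and physical assessments are conducted face-to-face at the University of Queensland" and "Physical assessments are conducted by an exercise physiologist and last for 30 minutes". The physical tests come directly after the cognitive session.
- **Exercise training.** Setting places the program at "a privately-owned gym in Brisbane, Australia". Under Exercise-only training, each session "is supervised by at least one qualified fitness instructor".
- **Cognitive training.** Under Exercise and cognitive training: "A graduate psychology student leads these sessions in a quiet room away from the main gym area".
- **Cognitive tests.** Modes of assessment assigns these to the first author. The Aim section says of the same person: "An exercise training program and a cognitive training program have been developed by the first author".

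Measurements lists aerobic capacity and strength among the primary outcomes, alongside cognitive functioning.

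**The concern.** Participants and instructors cannot be masked in a trial of supervised exercise against no training. The person who measures the physical outcomes is in a different position. As described, that person has a different role from the training staff and works at a different site. A waiver covering every researcher therefore goes further than the described logistics appear to need.

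The exposed measures matter because they are primary. The walk score is a distance reached by effort, and the chair stand and arm curl scores are counts of repetitions in 30 seconds. An assessor who knows the group can encourage one arm more, or accept a borderline repetition more readily, without intending to. The first hypothesis in the Discussion compares both trained arms with the control arm on such measures. A push in one direction in the trained arms would look like a training effect. Randomisation does not remove it, and the planned analysis of variance cannot separate it from a true effect.

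**Working it through.** **Step 1. Does the described work require the physical assessor to know the group?**

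| Task | Who | Where | Section |
|---|---|---|---|
| Exercise sessions | Fitness instructor | Private gym | Setting; Exercise-only training |
| Cognitive training | Graduate psychology student | Room away from the main gym area | Exercise and cognitive training |
| Cognitive tests | First author, who developed both programs | University | Aim; Modes of assessment |
| Physical tests | Exercise physiologist | University | Modes of assessment |

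The physiologist appears only in the last row. Nothing in the article gives this role a part in allocation or training. That is an argument from the described roles: the article does not state that the physiologist is independent of delivery, and it does not say who carries out the strength assessment in the first gym session.

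**Step 2. Which physical primary outcomes are exposed?**

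- Six-Minute Walk: metres walked, dependent on effort. Exposed.
- 30-Second Chair Stand: count of full stands. Exposed to encouragement and to what is accepted as full.
- Arm Curl: count of curls. Exposed in the same way.
- Modified Astrand-Ryhming cycle test: sub-maximal, work-rate adjusted by heart rate and age, maximal oxygen uptake read from a nomogram. Less exposed.

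**Step 3. The plan's own sample size.**

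The Sample size section gives 29 per group for a 118.8 ms difference (SD 160) on Choice Reaction Time, two-tailed alpha 0.05, power 80%.

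- Standardised difference: 118.8 / 160 = 0.7425.
- n = 2 × (1.960 + 0.842)² / 0.7425² = 28.5, so 29 per group. Power with 29 is 80.7% by the normal formula and 79.3% by the t-test.
- Attrition: 29 / 0.9 = 32.2, so 33 per group; 3 × 33 = 99.

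The stated figures reproduce. Masking the assessor changes none of them.

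**Step 4. What an assessor shift would do (illustration).**

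The documents give no size for assessor bias, so the shift b, in SD units, is assumed. With no true effect, a two-sample t-test with n per arm has a non-central t distribution with 2n − 2 degrees of freedom and non-centrality b × √(n/2). For n = 29, √(29/2) = 3.808, there are 56 degrees of freedom and the critical value is 2.003.

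| Assumed shift b | Non-centrality | Rejection rate, 29 per arm | Rejection rate, 33 per arm |
|---|---|---|---|
| 0.1 SD | 0.381 | 6.6% | 6.9% |
| 0.2 SD | 0.762 | 11.6% | 12.6% |
| 0.3 SD | 1.142 | 20.2% | 22.5% |

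The normal approximation for 29 per arm gives 6.7%, 11.9% and 20.8%, so the result does not depend on the formula used.

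**The case against.** **The open design is disclosed.** The article states plainly that nobody is masked and does not contradict itself. This stands: the point is an avoidable design weakness and not an inconsistency. Disclosure does not, however, reduce the bias.

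**The physiologist's independence is not stated.** A reader might infer from the separate sites and job titles that the physiologist has no contact with training or allocation, and so that masking certainly needs no extra staff. The article supports only the weaker statement that no such contact is described. It is a condensed account and the logistics may be set out elsewhere. This stands, and the fix allows for it.

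**Masking would be partial.** Participants know their group and may reveal it. Each physical test follows immediately on a session with the unblinded cognitive assessor. Participants' own effort stays influenced by their knowledge whoever holds the stopwatch. All of this stands. It limits the benefit but does not remove the case for masking the assessor.

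**The tests are standardised.** The chair stand and arm curl come directly from a published battery, and the use of adaptations is noted. This narrows the room for judgement over what counts. It does not standardise encouragement by someone who knows the group.

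**The error rates are hypothetical.** A reader might take 6.6% to 20.2% as the trial's actual false-positive rate. The documents do not support that. The shift is assumed, 29 per arm was derived for a computer-timed cognitive task, no physical outcome was sized, and the planned analysis covers three time points where the illustration uses one post-test comparison. The figures show only how fast the error rate rises if a shift exists.

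**The cognitive tests look at least as exposed.** A reader might extend the remedy to them by having coded record sheets scored later. Only one cognitive assessor is named, and that person ran the sessions and could recognise the responses. Reliable masking would need a second scorer, and bias during face-to-face testing would remain. The low-cost remedy therefore does not carry over.

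**Conclusion.** The point holds as an inexpensive improvement limited to the physical-test assessor. The Blinding section leaves that assessor unmasked by making no exception, and the roles described elsewhere give no reason why this person must know the allocation. Three physical primary outcomes are open to assessor influence in the comparison of trained arms with control; the cycle test is much less so.

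The conclusion rests on two assumptions: that the term researchers in the Blinding section includes the physiologist, and that the physiologist has no undescribed part in delivery or allocation. The size of any bias is unknown, and the documents do not show that it has occurred or will occur.

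**What to change.** Reword the Blinding section so that the exercise physiologist is masked to allocation at the 16-week and 40-week visits, and describe how:

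1. Withhold the allocation list from the physiologist.
2. Instruct participants before each of these visits not to mention their group, and instruct the cognitive assessor, whose session comes immediately before, not to disclose it.
3. Have the physiologist record a guess of each participant's allocation, so that the success of masking can be reported.

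If the physiologist does take part in training or allocation, state that as the reason why masking is not possible.

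The cost is protocol wording, a short instruction and one extra item on the record form. The sample size does not change, and no extra assessor is needed provided the roles are as separate as they appear. Masking will be incomplete where participants disclose their group. It leaves untouched any bias from participants' own effort and from the unblinded cognitive assessments, and the report should say so.

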### Intervention

#### Exercise-only training

Participants in this group receive three gym-based sessions per week for 16 weeks. Each session lasts for 60 minutes and includes progressive aerobic and strength training. Each session includes a maximum of 10 participants and is supervised by at least one qualified fitness instructor.

The progression of the aerobic training is adapted from the ACSM Guidelines for Exercise Testing and Prescription [51]. Intensity is prescribed using percentage of Heart Rate Reserve (HRR). Participants on medications which attenuate heart rate (e.g. beta-blockers) are prescribed exercise intensity using Rate of Perceived Exertion (RPE; [52]). The relative progressions of intensity and duration can be seen in Table 1. Intensity is monitored with Polar A3 heat rate monitors. Participants complete the aerobic training on treadmills, stationary bicycles, cross-trainers, and stationary rowing machines.

**Table 1 T1:** Duration and intensity progression of aerobic training

**Week**	**Duration (min)**	**Intensity (% HRR)**	**Intensity (RPE)**
1	20	50 – 60	9 – 11
2	20	50 – 60	9 – 11
3 – 5	25	60 – 70	11
6 – 8	30	60 – 70	11
9 – 11	30	70 – 80	11 – 13
12 – 14	35	70 – 80	11 – 13
15 & 16	40	75 – 85	13 – 15

Strength is assessed, and intensity prescribed, for each participant in the first gym session. Progress is monitored and prescribed by the fitness instructor. The strength training includes exercises to target major muscle groups in the upper body, lower body, and core. The upper and lower body exercises use free weights and machines. The core exercises use a swiss-ball.

Participants stretch major muscle groups at the end of each session.

#### Exercise and cognitive training

Participants in this group receive two gym-based exercise sessions and one cognitive training session per week for 16 weeks. Each session lasts for 60 minutes. The exercise training (including the progression of duration and intensity) is identical to that received in the Exercise-Only Group. The cognitive training program includes three modules, covering memory, executive functioning, and mental speed. Each session follows the same format:

(1) theoretical overview

(2) outline of 'everyday' applications

(3) practice activities

Introductory and revision sessions are conducted at the beginning and end of the program. Table 2 outlines the content of each session. A graduate psychology student leads these sessions in a quiet room away from the main gym area.

**Table 2 T2:** Cognitive training program outline

Module	Session	Content
Introduction	1	Aging, Cognitive Functioning, Program Overview
		
Memory	2	Introduction to Memory
	3	Chunking, Organisation, Visualisation
	4	Storytelling, Method of Loci, Mnemonics
	5	Keywords, Association
		
Executive Function	6	Introduction to Reasoning
	7	Pattern Identification
	8	Concept Formation, Verbal Fluency
	9	Attention, Mental Flexibility
		
Information Processing	10	Introduction to Speed of Information Processing
	11	Simple Speed
	12	Choice Response Speed
		
Revision	13	Memory
	14	Executive Function
	15	Speed of Information Processing
	16	General

#### Control group

Participants in this group receive no formal intervention. They are contacted by telephone at Week 4 and 12 to check continued completion of the weekly diary. At Week 8 each participant is posted a cinema voucher and a letter to thank them for their ongoing involvement.

### Adherence and compliance

Attendance at each cognitive training session is recorded by the instructor. At each exercise training session, participants are provided with individual diaries in which to record the date and the intensity and duration of each activity undertaken in that session. All participants (including control participants) are provided with a weekly diary in which to record physical, social and cognitive activities undertaken outside the program.

### Assessment protocol

#### Assessment stages

In addition to screening, assessments are conducted at baseline (0 weeks), 16-weeks (post-test), and 40 weeks (6-month follow-up).

#### Modes of assessment

Screening is conducted by telephone. Cognitive and physical assessments are conducted face-to-face at the University of Queensland. Cognitive assessments are conducted by SO. Each cognitive assessment session lasts for 90 minutes. Physical assessments are conducted by an exercise physiologist and last for 30 minutes. Physical assessments are conducted immediately after the cognitive assessments. Self-administered questionnaires are used to assess psychological wellbeing. These are provided after the cognitive assessment, with participants instructed to complete them at home and mail them back within seven days using a provided reply-paid envelope. Participant perceptions of the two training programs are collected using a feedback form included with the other self-report instruments. Only training participants complete this feedback form.

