### Linking exercise and cognitive functioning

Several mechanisms have been suggested to explain the relationship between exercise and cognitive functioning. The main hypothesis is that exercise directly affects the structure and function of the brain. Increases in aerobic capacity (as a result of increases in exercise) are thought to increase cerebral blood flow, improve the transport and utilization of oxygen and glucose in the brain, promote neurogenesis (the creation of new nerve cells), and regulate neurotransmitter synthesis [14,15,17,18,26-28]. Some studies have found an association between improvements in aerobic capacity and improvements in cognitive function [19,21]. Other studies, however, have found no relationship [22-24,29]. More evidence is required to validate the idea of increased aerobic capacity as a prerequisite for improved cognitive functioning.

Psychological factors may play a role in mediating the relationship between exercise and cognition [30]. Exercise is known to improve psychological well-being [31], and psychological well-being has been associated with cognitive functioning [32,33]. A few studies of exercise training and cognitive training have included psychological measures (e.g. [22,34-38]), but results have been mixed. More research is required to elucidate the mediating role of psychological factors in the exercise-cognition relationship [30].

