### Randomization

Participants are randomly allocated using block randomization [50]. Each block contains one exercise-only group allocation, one combined exercise *and *cognitive training group allocation, and one control group allocation. The order of the groups within each block is randomly generated by selecting papers from a box. The box contains three papers marked *Exercise Only*, *Exercise & Cognition*, and *Control*, respectively. This process is repeated to generate a list of 25 blocks. Each time a participant meets the eligibility criteria and screening requirements, they are allocated to the next available place on the list.

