### Measurements

The primary outcome measures are indicators of cognitive functioning, aerobic capacity and strength. Secondary outcome measures are anthropometric measurements, resting heart-rate, blood pressure, indicators of psychological well-being and participant perceptions. All measures are assessed at baseline, post-test, and 6-month follow-up, except for the qualitative feedback which is assessed only at post-test.

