#### Secondary outcome measures: Psychological well-being

##### Memory Complaint Questionnaire (MAC-Q)

This is a six-item scale of self-reported memory decline [66]. Participants rate current memory ability against past performance for given situation (e.g. remembering the name of a person just introduced to you), on a 5-point scale from *much better now *to *much worse now*. The scale reliability is .57, with test-retest reliability of .67 [66]. Scores are summed, with double weighting for the final item (a comparison of general memory abilities). A higher score indicates greater self-reported decline.

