##### Goldberg Anxiety and Depression Scale (GADS)

This is an 18-item measure of symptoms of anxiety and depression, derived from psychiatric interview protocols [69]. Participants answer *Yes *or *No *to questions about their feelings in the past month, such as *have you been irritable? *and *have you felt hopeless? *The scale has been validated against clinical diagnoses of anxiety and depression, and found to have good specificity and sensitivity [69]. Higher scores reflect increased symptoms of anxiety and depression.

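### Baseline well-being forms may be completed after training has begun, and the same-wave regression cannot show that well-being influences cognition

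*Protocol article*

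**What the plan says.** The four self-report well-being instruments (MAC-Q, SF-36 Mental Health, GADS and the HRHS Control subscale) are secondary outcomes. Under Modes of assessment: "These are provided after the cognitive assessment, with participants instructed to complete them at home and mail them back within seven days". Under Measurements, the same schedule holds at every wave: "All measures are assessed at baseline, post-test, and 6-month follow-up, except for the qualitative feedback which is assessed only at post-test".

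The Assessment stages section gives the waves: "assessments are conducted at baseline (0 weeks), 16-weeks (post-test), and 40 weeks (6-month follow-up". Both training programs run for 16 weeks at three sessions per week (Intervention).

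On allocation, the Randomization section says: "Each time a participant meets the eligibility criteria and screening requirements, they are allocated to the next available place on the list". It does not say whether this comes before or after baseline testing. The Blinding section adds that "participants, researchers, and instructors are not blind to the allocation of participants".

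On purpose, the Background says: "Psychological factors may play a role in mediating the relationship between exercise and cognition". Aim 4 and hypothesis 4 speak only of associations. The Analyses section, however, words the regression directionally, as the influence of well-being change on cognition. It states no lag or wave.

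**The concern.** A baseline measure should be fixed before the intervention can affect it. Here the return window opens at the baseline visit and runs for seven days, and no rule ties its end to the start of training. A participant who follows the instructions exactly could fill in the baseline form after attending training. That can happen in the two training arms but not in the control arm, so the error would differ by arm. Self-reports from participants who know their allocation are the measures most exposed to it.

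The baseline value enters every change score. Two things are therefore at stake: any between-arm comparison of change in well-being, and the aim 4 regression that uses those changes.

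A second, smaller issue is the order within a wave. Cognition is tested first and well-being rated afterwards. A regression relating the two changes over the same interval has no time order in which well-being comes first, so it cannot support the directional wording in the Analyses section.

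**Working it through.** The plan gives no figure for this point, so there is none to reproduce. The check is timeline arithmetic on the stated schedule.

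**Inputs.** Waves at weeks 0, 16 and 40 (Assessment stages). Return window of 7 days (Modes of assessment). Three sessions per week for 16 weeks in each training arm: three exercise sessions, or two exercise plus one cognitive (Intervention). GADS recall: "Participants answer *Yes *or *No *to questions about their feelings in the past month". Not stated: the gap, g days, between the baseline visit and the first session. I take a month as 30 days.

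**1. Overlap at baseline.** Total sessions = 3 × 16 = 48. The overlap is max(0, 7 − g) days.
- g = 0: 7 days, so up to 3 of 48 sessions = 6.25%.
- g ≥ 7: zero.

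Read literally, week 0 + 16 training weeks = week 16, which leaves no slack. The week labels are nominal, however, so g = 0 is the worst case and not a derived fact.

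**2. Effect on change scores.** Let p be the share of training-arm participants who complete the baseline form after training has started, and δ the mean shift in their score caused by that early experience. The training arm's mean baseline moves by p × δ, the control arm's by 0. The between-arm difference in mean change is then off by −p × δ. The documents give neither p (anywhere from 0 to 1) nor δ, so neither size nor direction can be fixed. An early lift in mood, for example, would shrink the measured improvement.

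**3. GADS at baseline.** At g = 0 and completion on day 7, 7/30 = 23% of the recall window falls after the start of training and 23/30 = 77% before it.

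**4. Order within and across waves.**
- Within a wave, well-being follows cognition by 0 to 7 days. That is at most 7/112 = 6.3% of the 16-week interval (16 × 7 = 112 days) and 7/168 = 4.2% of the 24-week interval from post-test to follow-up (24 × 7 = 168 days).
- Across waves the order reverses. Week-16 well-being, returned by about week 17, precedes week-40 cognition by about 23 to 24 weeks.

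**The case against.** The strongest reply is that the overlap is hypothetical. No section states when training starts relative to the baseline visit. Training runs in supervised groups of up to 10 and one assessor conducts every 90-minute cognitive session, so a gap is plausible. A return-before-training rule might also sit in fuller study procedures. This stands as far as it goes: the overlap is possible, not certain. But the article does fix the seven-day rule, and nothing in it stops a compliant form from being completed late.

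A reader might infer several stronger things that the document does not support:

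- **That the proposed mediator is always measured after the outcome.** This is true only within a wave; week-16 well-being comes well before week-40 cognition. A lagged analysis is therefore available, though none is stated and it would cover the period after training ends.
- **That the trial claims to establish mediation.** Mediation appears as background rationale. Aim 4 and hypothesis 4 claim association.
- **That test experience distorts the ratings, above all on MAC-Q, described as "This is a six-item scale of self-reported memory decline".** This is conceivable, since it follows memory tests. But no section says that scores are fed back, the form may be completed days later, and the order is the same in every arm. An effect specific to the arm taught memory strategies is conjecture.
- **That controls cannot be affected at all.** Only training experience is confined to the training arms. Knowing one's allocation can colour answers in any arm.
- **That all forms should be moved ahead of the cognitive tests.** Questions on memory complaints and mood could then prime a primary outcome. Completing forms in the week before post-test would, on the same no-gap timeline, place them in training week 16 with up to 3 of 48 sessions still to come. Same-wave changes would remain concurrent in any case.

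**Conclusion.** The concern holds in limited form. The stated procedure allows baseline well-being to be recorded after training has begun, in the training arms only. The exposure runs from zero (gap of seven days or more) to at most 3 of 48 sessions (training starts immediately). The resulting bias cannot be sized from the document, because neither the number of late completers nor the effect of early sessions on the scores is given.

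It reaches the secondary well-being outcomes and aim 4. It does not touch the primary group comparisons on cognition, aerobic capacity and strength, which are measured face to face at the visit.

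Separately, the same-wave regression of cognitive change on well-being change can show an association only; the directional wording in the Analyses section goes further than the design allows. Both points are small, but the first cannot be fully repaired in analysis once the forms have been collected late, and it is cheap to prevent.

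**What to change.** 1. In Modes of assessment, require the baseline questionnaires to be completed and returned before the first training session, or completed on site after the tests. Where possible, have them completed before allocation is disclosed.
2. Keep the cognitive tests before the questionnaires, to avoid priming the primary outcome. The seven-day home return can stay for post-test, follow-up and the program feedback form.
3. In Analyses, describe the same-wave regression of cognitive change on well-being change as an association.

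The cost is a wording change, with no new visit or instrument. Some participants would spend a few extra minutes on site, after a visit that already takes 90 + 30 = 120 minutes, or would start training slightly later while a form is awaited.
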